## Discussion

The subjective and functional outcome of operatively treated ankle fractures is often poor [5, 6]. Winters et al. reported moderate to poor results in more than 20 % of their patients in simple, isolated fractures of the distal fibula [35]. Furthermore, Day et al. demonstrated in their long-term study, that only 52 % of the patients had good to excellent results following a bimalleolar fracture whereas 48 % of these patients only had a moderate or poor outcome after 10 years [36]. Hong et al. showed that more than 50 % of the patients with bi- or trimalleolar fractures suffered from stiffness and pain after 2 years. In the same collective 18 % did not return to sports after this period of time [37]. Recently, several determining factors for these unsatisfying results have been proposed including age, sex, severity of the fracture, size of the posterior fragment, involvement of the medial malleolus and the quality of anatomic reduction [36, 38–42]. The prerequisite for a satisfactory outcome is the anatomic reduction – at the same time it is the only risk factor that can surgically be influenced. But even anatomic restoration cannot surely prevent poor postoperative results. Based on these considerations, the unrecognized articular injuries involving cartilage and soft tissue might be the reason for these adverse clinical results [2, 8, 9]. Only since arthroscopic studies in ankle fractures exist, the incidence of chondral lesions has become evident. Chondral lesions occur in 20–89 % [3, 15]. A recent review reported chondral lesions in 495 of 782 patients (63,3 %) with more than a half of these lesions localized on the talus [43]. For instance, Hintermann et al. reported 79 % osteochondral lesion (OCL) in acute ankle fractures [5]. Leonartidis et al. found comparable rate of OCLs in their retrospective case series of 83 patients [44]. In their prospective study Stufkens et al. could demonstrate that the traumatic cartilage injury was an independent predictor for the development of posttraumatic osteoarthritis. Further they could show that chondral lesions on the lateral talus and medial malleolus were associated with worse clinical outcome [45]. Until today, there are only two randomised controlled trails evaluating the effect of additional ankle arthroscopy in ankle fractures. In contrast to our study, both studies available only included patients with isolated fractures of the distal fibula at the level of the syndesmosis (AO type 44 B1). These are the most simple fractures that are regularly treated operatively. Thodarson and co-workers found in their very small cohort that eight of nine patients had articular damage to the talar dome in the arthroscopy group [3]. They found better results in favour of AORIF although not significant after 21 months of follow-up [3]. Takao et al. enrolled 72 patients in total with 36 for each group with a follow-up of 3.5 years on average. They documented an osteochondral lesion in 74 % in the AORIF group. Furthermore, the mean AOFAS score was significantly better when patients were treated arthroscopically although the mean difference in AOFAS score was only 3.4 points [1].

Although arthroscopy is increasingly used in the setting of trauma for articular and periarticular fractures of the lower limb, the effectiveness of AORIF compared with ORIF has yet to be determined [46]. To date, currently available literature has not sufficiently proven that treatment of these intra-articular injuries improves outcomes over standard ORIF, as there is only few randomized controlled studies available comparing these two operative techniques. This also applies for fractures to the ankle joint - especially in case of complex fracture patterns - although the intra-articular damage is reported to be even more pronounced the more complex the fracture is [44].

Consequently, we perform the first RCT comparing AORIF to ORIF in complex ankle fractures expecting an even more distinctive effect of arthroscopy in these fracture types. By reporting the results of this first randomised controlled trail, we intend to document on the effectiveness of supplementary ankle arthroscopy in complex fractures to the ankle. By arthroscopically assisted fracture treatment we hope to improve the postoperative subjective and functional results. We believe this is of great importance as these injuries are frequent and debilitating. The main goal of our study is to identify the fracture types that will benefit from additional arthroscopy most.

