### Statistical analysis

Primary outcome of our study is the difference of the AOFAS score between the intervention (AORIF) and comparison (ORIF) group after a follow-up of 2 years. We expect a mean difference of four points between the AORIF and ORIF group showing better results in the AORIF group. This expectation is feasible on the basis of the existing data (see [3] and [1]). The statistical calculation was performed with an expected correlation of 0.5 between the two groups. Based on a conservative estimation of the observed standard deviation of the AOFAS score in a comparable population (see [3] and [1]), we expect a standard deviation of six for the AOFAS score in our population. Based on the supposed correlation of 0.5 the standard deviation of the differences regarding our primary outcome is also expected to be not more than six. Therefore, each group has to contain 37 patients in order to find a difference of four between the two groups with a level of significance of 5 % and a power of 80 % and a standard deviation of six. In case of subgroup analysis, Shapiro-Wilk and Levene tests will be used to test normality and equality of variances. Subgroup analysis will be conducted using Student’s t-test, Pearson Chi-Square or ANOVA where appropriate. Statistics will be calculated using SPSS 22.0 (SPSS Inc. Chicago, Illinois 60606).

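### The declared main goal, finding which fracture types benefit most from arthroscopy, is beyond a trial sized only for the overall AOFAS difference

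*Protocol article*

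**What the plan says.** Two places in the protocol article set the trial's target.

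- **Statistical analysis:** "Primary outcome of our study is the difference of the AOFAS score between the intervention (AORIF) and comparison (ORIF) group", with the time point set at 2 years. The sample size rests on this contrast: "We expect a mean difference of four points between the AORIF and ORIF group", and "we expect a standard deviation of six for the AOFAS score in our population". With 5% significance and 80% power the section arrives at 37 patients per group.
- **Discussion, last paragraph:** "The main goal of our study is to identify the fracture types that will benefit from additional arthroscopy most".

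Eligibility (Abstract; Eligibility criteria and Table 1) covers seven AO 44 types: A2, A3, B2, B3, C1, C2 and C3.

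On subgroups, the Statistical analysis section has a conditional passage. Should subgroup analysis be done, normality and variances are checked, and then: "Subgroup analysis will be conducted using Student’s t-test, Pearson Chi-Square or ANOVA where appropriate". It does not say which subgroups are meant or which quantity is compared. The one analysis by fracture type that is described, under Arthroscopic findings, compares the frequency and distribution of chondral lesions between fracture types in the arthroscopy group. It is not a comparison of treatment effects.

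**The concern.** Asking which types benefit most is asking whether the AORIF–ORIF difference varies with fracture type, that is, whether there is a treatment-by-type interaction. This needs far more patients than the overall comparison, and the sample size calculation takes no account of it. None of the methods listed for subgroups is described as a test of whether benefit differs by type.

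At stake is what the trial may conclude. With the type question declared the main goal and nothing marking it as exploratory, a reader of the results could take the ranking of small-subgroup estimates as the trial's headline answer on which fractures gain from arthroscopy. At this size, chance would account for much of that ranking.

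**Working it through.** **Inputs.** From the Statistical analysis section: difference 4, SD 6, alpha 5%, power 80%, 37 per arm (74 in total). From the eligibility criteria: 7 AO types. Assumptions, because the documents give no distribution: patients spread equally over the subgroups, 1:1 within each, and all 74 evaluable.

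**1. The plan's own figure.** For a two-sided unpaired comparison, the noncentral t distribution gives power 0.797 at 36 per arm and 0.808 at 37. The stated 37 is reproduced, so the sample size is right for the overall difference.

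**2. Effect within one of seven types.** Per arm: 37/7 = 5.29.
- SE = 6 × √(2/5.29) = 3.69.
- Power for 4 points: 16% (noncentral t); 19% by the normal approximation.
- Difference detectable with 80% power: 11.7 points (t) or 10.3 (normal), against 4 planned.

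**3. Difference in effect between two subgroups.** With m patients per arm in each subgroup, SE = 6 × √(4/m). Two-sided power for a true 4-point difference in effect, normal approximation:

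| Comparison | m | SE | Power |
|---|---|---|---|
| Two of seven types | 5.29 | 5.22 | 12% |
| Two of three AO groups (A/B/C) | 12.33 | 3.42 | 22% |
| Two halves of the trial | 18.5 | 2.79 | 30% |

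Even the most favourable split, two equal halves, would need 16 × ((1.96 + 0.84) × 6/4)² ≈ 283 patients for 80% power.

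**4. Spread of the estimates when all types benefit equally.** With a true effect of 4 in every type and SE 3.69, simulation (200,000 runs) gives an average largest estimate of 9.0 and an average smallest of −1.0. In 65% of runs at least one type shows no benefit or apparent harm.

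**5. Picking the best type when one truly is best.** If six types gain 4 points and one gains more, that one ranks first in 27% of runs with 2 extra points, 44% with 4 and 78% with 8. Pure chance would give 1/7 = 14%.

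**6. False positives, if the subgroup sentence were applied as seven separate tests.** With no effect in any type:
- any significant result: 1 − 0.95⁷ = 30%;
- a significant result in favour of AORIF: 1 − 0.975⁷ = 16%.

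**The case against.** The strongest reply is that this is one closing sentence of a Discussion. The overall comparison is stated consistently in the Abstract, Study design, Primary outcome and Statistical analysis sections, and the same Discussion paragraph also says the trial is meant to document the effectiveness of arthroscopy. The sentence changes neither the primary outcome nor the sample size nor the data collected. That is true, and it is why the repair is cheap. But the sentence names the main goal without qualification, and it is a different goal from the one the trial was sized for.

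A second reply is that interaction terms, groupings and exploratory labels are commonly left to an analysis plan, which is not shown. That also stands, so the point does not rest on their absence. It rests on the conflict between two stated aims and on the sample size, and no analysis plan can remove either.

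Three stronger readings are tempting and are not supported:

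- **A reader might infer that the plan prescribes seven separate within-type tests.** It does not. The subgroup sentence is conditional, does not mention fracture type, may refer to the chondral-lesion comparison, and lists ANOVA, which could carry an interaction term. The 30% and 16% figures therefore apply only if the sentence is used in that way.
- **A reader might infer that the trial is bound to name a best type by chance.** Some type will always have the largest estimate, but it is a pure chance product only if effects are equal across types. The Background notes that osteochondral lesions become more frequent with fracture complexity, so the authors may expect unequal effects. A type with 8 extra points would usually be ranked first.
- **A reader might infer that 37 per arm is wrong.** It is right for the overall comparison.

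**Conclusion.** The point holds as an inconsistency with a real consequence: the main goal declared in the Discussion differs from the primary outcome in the Statistical analysis section and cannot be met with 74 patients. A 4-point difference in effect would be shown with about 12% to 30% power, depending on whether types, AO groups or halves are compared, and a 4-point effect within a single type with about 16%.

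These figures rest on the plan's SD of 6, equal spread over subgroups and complete follow-up. Unequal spread would help the commoner types and make the rarer ones worse. No plausible split makes the type-level question answerable at the effect size the plan expects. The primary comparison itself is unaffected.

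**What to change.** - **Discussion, last paragraph:** reword so that the main goal is the overall AORIF–ORIF difference in AOFAS at 2 years, as in the Statistical analysis section, and label fracture-type effects exploratory.
- **Statistical analysis:** for any comparison of treatment effect by fracture type, specify one model of AOFAS with treatment, AO group (A/B/C) and their interaction. Report the interaction test and the three group effects with 95% confidence intervals.
- **State the limit:** this analysis has low power, about 22% for a 4-point contrast between two equal groups. It does not rescue the type-level goal either; it only reports the evidence in the right form.
- **Rule on claims:** make no claim that one type benefits more than another on the basis of separate within-type p-values.

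The cost is a change of wording and one regression model, with no new patients or data. The downside is a more modest subgroup claim.

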## Ethics and consent to participate

This study is conducted according to the principles of the Declaration of Helsinki (Version 9, 10/08, Seoul) and in accordance with the Medical Research Involving Human Subjects Act. The Ethical Committee of the Medical Faculty approved the study at the Department of Trauma Surgery of Munich University Hospital (AZ 500-15). All patients included in our study provided written informed consent to participate.

## Consent for publication

Not applicable.

## Availability of data and material

As this is a study protocol, no data are presented.

## Abbreviations

AOFAS Score: American Orthopaedic Foot and Ankle Society
AORIF: arthroscopically assisted open reduction and internal fixation
ICRS: International Cartilage Repair Society
JSSF Score: Japanese Society of Surgery of the Foot
NIH: National Institute of Health
OCL: osteochondral lesion
OMAS: olerud and molasnder score
ORIF: open reduction and internal fixation
PITFL: posterior inferior tibio fibular ligament
RCT: randomised controlled trial
SF-12: a 12-item short-form health survey
TAS: tegner activity scale
VAS: visual analogue scale
